### Study procedures

#### Informed consent procedures

It is the responsibility of the investigator, or appropriate Good Clinical Practice (GCP) trained person delegated by the investigator as documented in the site delegation log, to obtain written informed consent from each participant prior to any participation/study-specific procedures. This should follow adequate explanation of the aims, methods, anticipated benefits and potential hazards of the study. The participants will be given ample time to consider giving their consent for the study. For this study a minimum of 24 hours will be given during which the consenting team will be contactable over the phone to answer any questions. The date on which the participant information sheet (PIS) is given to the participant must be documented within the patient’s notes to confirm that sufficient time was given. The investigator (or other qualified person) will explain to the potential participant that they are free to refuse any involvement with the study or alternatively withdraw their consent at any point during the study and for any reason. If there is any further safety information which may result in significant changes in the risk/benefit analysis, the PIS and informed consent form (ICF) will be reviewed and updated accordingly. All participants that are actively enrolled on the study will be informed of the updated information and given a revised copy of the PIS/ICF in order to confirm their wish to continue on the study.

#### Screening procedures

Patients will have undergone the below procedures as per standard of care which will in turn feed in to the investigator for their review prior to approaching the potential participant.OSDI Score >33; orOxford corneal staining grade ≥2; orSchirmer’s test without anaesthesia <5 mm at 5 min.

The results from these will be reviewed by the investigator prior to approaching the potential participant.

#### Randomisation procedures

Randomisation will be carried out by the Anglia Ruskin Clinical Trials Unit (ARCTU) using the SEALED ENVELOPE randomisation service. SEALED ENVELOPE is a randomisation and online database service developed for clinical trial services. It is an internet-based system and will be set for this study by ARCTU in accordance with the protocol. Enrolled patients will undergo 1:1 block randomisation to Arm A or Arm B. The system stores the predetermined sequence of randomisation and this list is visible to neither the investigator nor the ARCTU staff. Once a patient has consented to take part in the trial, they will be randomly allocated either to Arm A to receive FAB and conventional therapy or to Arm B to receive conventional therapy only. The research nurse or fellow or designated staff will log on to a web browser application and enter the patient’s eligibility factors into the system. The treatment allocation will be sent to the research team who will make the necessary arrangements for the patient’s treatment plan.

The treating ophthalmologist in the clinic will prescribe and counsel all patients on the correct technique for conventional treatment. The unblinded research nurses will provide additional training to the patients on the method of delivering FAB, including the use of a training video. Patients will be advised by the research team to inform their ophthalmologist if they have been started on any new treatment during the trial period by other clinicians or themselves.

### End of study definition

The definition of the end of study will be the point where the last patient recruited had the last follow-up visit.

### Participant withdrawal

Patients will be withdrawn from study based on the following:New diagnosis of infection on finger or eye.Requesting to be withdrawn for other reasons such as inconvenience of increased clinic visits.Pregnancy after recruitment.Systemic infection, or systemic antimicrobials for infection.If finger sore from repeated prick and patient does not want to use another finger.

Any adverse effects will be reported back to the lead investigator at the site and, if necessary, the patients.

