### Data analysis

Detailed data validation will examine completeness, existence and accuracy of collected data to assess data quality and identify missing and conflicting data. Statistical analysis will be performed on an intention-to-treat basis ie, inclusion of patients randomly assigned, regardless of adherence, actual treatment received, and subsequent withdrawal of treatment and/or deviation from the protocol and per-protocol (ie, inclusion of those who completed the treatment as planned)^29^ and will be reported according to 2010 CONSORT guidelines.^30^ All statistical analyses will be completed using SPSS Statistics V.22.0.^31^ A value of p<0.05 will be accepted as statistically significant. Conforming to recommendations for feasibility studies, data analysis will be primarily descriptive, with means, SD and frequency counts calculated for all variables of interest.

Exploratory efficacy analysis will compare the primary outcome variables derived from the data collected at 8 weeks between the two arms using a marginal general linear model with robust standard errors, to allow for clustering by group. Secondary outcomes between the intervention and control groups will be compared at 4 weeks, 8 weeks and 12 weeks (4 weeks post-treatment). Safety outcome measures will include IOP rise and any reported infection. Secondary analyses of the primary outcome, controlling for baseline covariates, will be performed using proportional hazards regression models.^32^ Analysis of treatment discontinuation adjusted for clinical site, baseline status, and whether the patient is randomised to the FAB or control (conventional treatment only) group will be conducted. Any interaction between baseline status or regimen and treatment will also be assessed. Interactions between significant covariates and treatment effects will be assessed in the context of the proportional hazards models.

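### The withdrawal rule takes patients out of the study, not only off FAB, so secondary outcomes needed for the intention-to-treat comparison may be lost in a way related to arm and tolerability

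*Protocol article*

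**What the plan says.** The Participant withdrawal section of the protocol article states its rule at the level of the study: "Patients will be withdrawn from study based on the following". Of the five listed reasons, one concerns the FAB procedure itself: "If finger sore from repeated prick and patient does not want to use another finger". Another is "New diagnosis of infection on finger or eye". The remaining three are patient request, pregnancy, and systemic infection or its treatment. The request item reads "Requesting to be withdrawn for other reasons such as inconvenience of increased clinic visits", which suggests that withdrawal is understood to end the visits.

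The Data analysis section defines intention-to-treat as "inclusion of patients randomly assigned, regardless of adherence, actual treatment received, and subsequent withdrawal of treatment and/or deviation from the protocol" and compares secondary outcomes at weeks 4, 8 and 12, the last being four weeks after treatment ends. The same section says "Safety outcome measures will include IOP rise and any reported infection".

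The Outcome assessment section lists self-reported adherence and study completion as separate parts of the primary feasibility outcome. The section on notification and reporting of adverse events says that the research team follows up a participant who has a non-serious event. No section says whether the scheduled outcome visits continue once a patient has been withdrawn.

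**The concern.** Stopping a treatment and leaving a trial are different events. A patient whose fingers are sore and who declines to prick another one has declined FAB, but has not necessarily declined an eye examination at week 8. The article makes the first event trigger the second.

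Three things are at stake:

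- **Secondary outcomes.** An intention-to-treat comparison that disregards adherence needs outcomes from patients who stopped. If their visits end, the comparison falls back on those who stayed, and staying may depend on arm and on how well FAB was tolerated.
- **Feasibility information.** A definitive trial needs to know both how many patients stop FAB and how many of those would still attend. The rule merges the two, because stopping for a listed reason counts automatically as not completing.
- **The planning SD.** The Sample size section wants parameters such as the SD for the next trial. Under this rule the FAB-arm estimate would come disproportionately from patients who tolerated FAB.

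**Working it through.** **1. Which reasons can occur in which arm**

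| Listed reason | Arm A (FAB) | Arm B |
|---|---|---|
| Sore finger, declines another | Yes | No |
| Finger infection | Yes, plausibly more often | Yes |
| Eye infection | Yes | Yes |
| Patient request | Yes | Yes |
| Pregnancy | Yes | Yes |
| Systemic infection or antimicrobials | Yes | Yes |

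One reason is confined to Arm A, and the article foresees it: its strengths-and-limitations list warns of finger soreness in the intervention arm. Finger infection is plausibly linked to FAB. The others can arise in both arms. No rates are stated.

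**2. What is lost**

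If visits end at withdrawal, a patient withdrawn before week 4 contributes no post-baseline secondary outcome. One withdrawn between weeks 4 and 8 lacks weeks 8 and 12. One withdrawn after week 8 lacks week 12.

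**3. The plan's own attrition figure**

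Inputs from the Sample size section: 52 patients (26 per arm), 10% attrition, target 60.

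- Inflated sample: 52 / (1 − 0.10) = 57.8, rounded up to 58. The stated 60 is consistent with this.
- Expected remaining: 60 × 0.90 = 54, which is at least 52.
- Expected losses: 0.10 × 60 = 6.

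**4. Illustrative size of the shift**

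Assumptions, none of them from the article: no data after withdrawal, analysis of available cases, and withdrawn patients worse than those who stay by d = 0.5 to 1.0 SD in either arm. The 1:1 allocation gives n = 30 per arm.

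In one arm, the mean of those who stay exceeds the mean of all randomised by (w / n) × d, where w is the number withdrawn. The between-arm shift towards FAB is therefore

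shift = (w_A − w_B) / 30 × d

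| Losses A, B | Remaining A, B | d = 0.5 | d = 1.0 |
|---|---|---|---|
| 3, 3 | 27, 27 | 0 | 0 |
| 6, 3 | 24, 27 | 3/30 × 0.5 = 0.05 SD | 3/30 × 1.0 = 0.10 SD |
| 6, 0 | 24, 30 | 6/30 × 0.5 = 0.10 SD | 6/30 × 1.0 = 0.20 SD |

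The first and third rows use the plan's 6 losses. The second uses 9, which is 9/60 = 15%. With 6 losses all in FAB, that arm loses 6/30 = 20% and keeps 24, below the stated 26 per arm, although the total of 54 still meets 52. That row is the extreme split.

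**The case against.** Several arguments against the point have force.

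- **A reader might infer that the withdrawal rule contradicts intention-to-treat.** It does not. Intention-to-treat says who is analysed and in which arm. The withdrawal section excludes nobody from the analysis and discards no data already collected. The conflict is one of execution: the rule stops the collection of data that the analysis needs. Handling of missing data can properly sit in an analysis plan that is not shown, but no analysis plan can recover visits that sites were told not to hold.
- **A reader might infer that FAB failures disappear from the results.** For the primary outcome they do not. A withdrawn patient counts as a non-completer, and an analysis of treatment discontinuation that accounts for arm is planned. The loss concerns secondary efficacy outcomes and scheduled assessments such as IOP.
- **A reader might infer that the losses fall mainly on FAB.** This is plausible but not stated. One reason is confined to FAB, most can occur in either arm, and no rates are given.
- **A reader might infer that follow-up of infection is cut short.** This is not established. An infection is recorded when it triggers withdrawal, non-serious events are followed up by the team, and SAE reporting runs to four weeks after the intervention. What remains is that this provision stands unreconciled beside study withdrawal and does not preserve the scheduled visits.
- **The article is condensed.** It points to a detailed protocol in a supplementary file, which may say more. But the article does state a rule, and states it at study level. If the full protocol already continues visits, the point reduces to aligning the wording.
- **The secondary outcomes are unpowered and mainly descriptive.** This limits the harm. It does not restore the retention and SD information that the feasibility trial exists to supply.

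**Conclusion.** The point holds in a limited form. As written, the article turns some reasons for stopping FAB into exit from the study and provides for no outcome visits afterwards. That prevents full execution of the intention-to-treat comparison of secondary outcomes, which would be missing in a way that may relate to arm and tolerability. It also makes it impossible to tell whether patients who stop FAB would remain in follow-up.

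The direction and size of any bias are unknown. On the assumed values, the shift runs from 0 with equal losses to 0.10 to 0.20 SD towards FAB with 6 losses against 0. Expressing this as a percentage overstatement would need a true effect, which the article does not give. The primary feasibility counts are not biased by removal of failures, although their completion component loses meaning because it absorbs treatment intolerance.

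**What to change.** Reconcile the Participant withdrawal, Data analysis and adverse-event reporting sections by defining two events:

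1. **Stopping FAB**, with the clinical reasons left exactly as the investigators have set them.
2. **Withdrawal of consent to follow-up**, which alone ends data collection.

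After the first, state that the scheduled assessments at weeks 4, 8 and 12 and the adverse-event follow-up continue for patients who agree. Record the date and reason of each event separately on the CRF, and report the two as separate feasibility outcomes by arm.

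The cost is a minor amendment, CRF wording, and a few follow-up visits for patients who have stopped FAB. The article describes recruitment as still open, and missed visits cannot be recovered later, so the change is worth making promptly.

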### Notification and reporting AEs or reactions

No serious AEs (SAEs) or complications associated with use of FAB in the treatment of ocular disease has been reported by the literature. Preliminary results of a pilot study conducted by the authors and involving 16 patients with DED also demonstrated no adverse effects of using FAB in the eye for 2 months.^22^ Although, we do not envisage any SAEs with the intervention in this trial, if an AE occurs and is not defined as SERIOUS, the AE will be recorded in the study file and the participant followed up by the research team. The AE will also be documented in the participants’ medical notes (where appropriate) and the case report form (CRF). SAEs that are considered to be ‘related’ and ‘unexpected’ will be reported to the sponsor within 24 hours of learning of the event and to the main research ethics committee within 15 days in line with the required time frame. SAE reporting will commence at the start of the trial and up to 4 weeks after the intervention.

### Patient and public involvement

Patients who participated in a previous pilot (exploratory) study conducted by the study authors^22^ were involved in a focus group meeting and provided inputs on research design and study procedures. Two of the patients also participated in an advisory group for this trial and provided input on prioritising the research questions and also reviewed the study protocol and participant information resources. Patients in this trial will be invited to request study results from the research team if interested.

## Ethics and dissemination

Participant anonymity will be protected and maintained at all times. Information with regards to study participants will be kept confidential and managed in accordance with the Data Protection Act, NHS Caldicott Guardian, The Research Governance Framework for Health and Social Care and Research Ethics Committee Approval in the UK. Data obtained in the trial will be stored using a unique study code, which is non-identifiable and anonymised. Patients' personal data will be stored separately and confidentially by the participating sites and will not be entered into the trial database. All written information will stored in a locked filing cabinet in a locked room. Any web-based data will be stored in a secure password-protected and encrypted central database at ARCTU. Only individuals directly involved with the study will have access to trial data. Study participants will also be provided with the contact details of the trial team at the respective sites who will be able to answer any additional queries.
